### Exclusion criteria

emergency hip or knee replacement surgery, such as after a fallrevisions or exchange surgeryPatients already received a replacement of another joint in the pastcognitive impairments of all types (as assessed by the attending physician)mental illnesses of all types (as assessed by the attending physician)Patients, who have not downloaded the app when they were admitted to the hospital (intervention group)post-surgical complications, such as infections, allergies, instability, delirium, or otherlimited language skills preventing proper app use or completion of questionnaires

Participants assigned to the intervention group who failed to download or access the app will be excluded. However, project coordinators of the participating hospitals will interview those participants and record their reasons for not engaging with RECOVER-E. These data will be analysed and reported as part of the sample description.

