### Intervention group

Patients assigned to the intervention group will, in addition to standard care, receive the smart phone app “RECOVER-E” for iOS and Android devices. Immediately after the baseline data collection (4–6 weeks before surgery, t_0_) participants will receive an access link and instructions on how to download the app on different smartphones. Additionally, they have the possibility to get help from the project coordinators or via the study hotline. Patients register themselves with a personal ID and can immediately start using the app.

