### Data analysis

Baseline data, clinical and demographic characteristics will be presented to show the baseline comparability of the intervention group and the control group. The analysis will include all patients following the intention-to-treat principle, drop-out and loss to follow-up will be described. Data will be checked for completeness and normality. The treatment effect will be evaluated by the change in ADL using between group analyses, such as independent t-test and ANCOVA to adjust for demographic factors such as age, sex, BMI (body mass index), baseline pain, anxiety, joint, comorbidities, physical activity, pain medication, type and duration of rehabilitation and social support on change in outcomes. For comparison within groups paired t-tests will be conducted. Within the intervention group the relationship between usage metrics and patient reported outcomes will be analysed using linear regression analyses.

All statistical analyses will be performed using IBM SPSS Statistics for Windows, version 24 (IBM Corp., Armonk, N.Y., USA).

Results of the study will be presented at conferences and placed in journals.

The controlled trial will be accompanied by multi-perspective qualitative research approaches to understand user decisions and long-term user engagement of the intervention. These studies will be reported elsewhere.

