## Discussion

The aim of the study is to enhance patient reported outcomes after surgical hip or knee replacement by using mHealth with evidence-based content and interface.

It seems reasonable to bring patient education to the next level and adapt it to the needs and conditions of modern society. In recent years, the concepts of eHealth (Electronic Health) and mHealth have become increasingly important in patient-centred health care aiming to enhance patient involvement and self-management capabilities [19, 20]. mHealth intends to capitalize on people’s ubiquitous access to mobile phones to provide 24/7 health care [51]. Ideally, it leads to improved health outcomes by increasing patient knowledge, providing social support, enhancing patient-provider communication and saving resources at the same time [52].

However, there is a lack of evidence for the effectiveness of the use of mHealth in patients undergoing joint replacement [53, 54]. This study will investigate the effects of an evidence-based mobile app as an educational intervention on patient reported outcomes of this target group.

Numbers of joint replacements are increasing and shorter hospital stays require solid self-management skills. Evidence supporting the use of mHealth to potentially improve patient outcomes is of particular importance to open up new possibilities for patient care.

A major limitation of the study is the non-randomized assignment of participants. Therefore the comparability of the groups regarding all relevant patient characteristics will be comprehensively analysed.

A second limitation is a potential mode effect due to different survey modes (online based vs. tablet based) at baseline and 3 months post-surgery.

Another limitation and potential source of bias is the exclusion of participants assigned to the intervention group, but who failed to download or access the app. We have chosen to do this because those participants miss out on engaging with app contents for the preoperative phase that are expected to have an effect on primary and secondary outcomes. We will, however, analyse and report patients’ reasons for not engaging and consider this aspect regarding the generalisability of our findings.

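### Excluding intervention patients who do not download the app (and patients with complications) contradicts the intention-to-treat analysis and filters one arm after assignment

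*Protocol article*

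**What the plan says.** Three parts of the protocol article bear on who is analysed.

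- **Exclusion criteria.** The list contains "Patients, who have not downloaded the app when they were admitted to the hospital (intervention group" arm only), and the text below it repeats: "Participants assigned to the intervention group who failed to download or access the app will be excluded". Coordinators will interview these patients, and their reasons will go into the sample description. The same list excludes patients with post-surgical complications, in either arm.
- **Data analysis.** "The analysis will include all patients following the intention-to-treat principle".
- **Discussion.** "Another limitation and potential source of bias is the exclusion of participants assigned to the intervention group". The reason given is that "those participants miss out on engaging with app contents for the preoperative phase that are expected to have an effect on primary and secondary outcomes".

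On timing, the section with Fig. 1 assigns patients by the calendar period of their preoperative consultation. The section on the intervention group says that, directly after baseline, "participants will receive an access link and instructions on how to download the app on different smartphones". Download is then judged at hospital admission.

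The sample size section requires 58 knee and 58 hip patients. It recruits 160 to cover 20% dropout, 5% complications and 4% erroneous records.

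**The concern.** An analysis that keeps all assigned patients cannot also drop some of them for what they did, or what happened to them, after assignment. The download rule is the more serious of the two exclusions because it applies to one arm. Control patients must own a smartphone, but nothing tests whether they would have installed and used an app. The app arm is therefore narrowed to patients who engaged, while the control arm keeps its would-be non-engagers.

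The complication rule applies to both arms but is also judged after assignment. The app teaches complication prevention, so the exclusion need not be neutral between arms.

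The primary comparison is at stake. Allocation is already by calendar period rather than at random, and this adds a second, avoidable selection.

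**Working it through.** **1. Can the statements be reconciled?** In order, a patient is assigned by consultation date, completes baseline, receives the link, and is judged at admission. The download rule is therefore not an eligibility criterion. Reading "all patients" as those left after exclusion gives a treatment-received set in one arm, which is not intention-to-treat. The complication rule fails in the same way, since it can only be applied after surgery.

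**2. The article's own figures.** Difference 10, SD 15, power 0.80, α 0.05; sidedness is not stated.
- One-sided t-test: 29 per arm, so 58 per joint (power 0.81). This reproduces the article.
- Two-sided t-test: 37 per arm, so 74 per joint. With 29 per arm, power is 0.70.
- Inflation: 116 / (0.80 × 0.95 × 0.96) = 116 / 0.7296 = 159.0, in line with 160. The three stated losses use up the whole allowance.

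**3. Bias if the app has no effect.** Let f be the share not downloading and d the prognostic gap in ADL change (downloaders minus non-downloaders, without the app). Neither is in the article. I assume f = 10-30% and d = 0-10 points. With no app effect, the filtered app arm exceeds the full arm by f × d. The standard error is 15 × √(1/n + 1/(n(1−f))), with n controls: 29 per joint or 58 pooled. Type I error is by normal approximation, unadjusted and two-sided at 0.05.

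| f | d | Bias | Per joint (n = 29) | Pooled (n = 58) |
|---|---|---|---|---|
| any | 0 | 0 | 5.0% | 5.0% |
| 10% | 5 | 0.5 | 5.2% | 5.4% |
| 10% | 10 | 1.0 | 5.7% | 6.4% |
| 20% | 5 | 1.0 | 5.7% | 6.3% |
| 20% | 10 | 2.0 | 7.7% | 10.4% |
| 30% | 5 | 1.5 | 6.4% | 7.8% |
| 30% | 10 | 3.0 | 10.6% | 16.5% |

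For example, at f = 20%, d = 10 and n = 58, the standard error is 15 × √(1/58 + 1/46.4) = 2.95 and the shift is 2.0 / 2.95 = 0.68 standard errors.

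**4. If the app works.** Suppose users gain 10 points and non-users nothing. The filtered estimate is 10 + f × d, so 10 to 13. The effect across all assigned patients is 10 × (1 − f), so 9, 8 or 7 at f = 10, 20 or 30%. The two differ even when d = 0.

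**5. Numbers lost if the exclusion stays.** At f = 20% the evaluable app arm is 80 × 0.7296 × 0.8 = 46.7 instead of 80 × 0.7296 = 58.4, or about 23 against 29 controls per joint. Power for 10 points (t-test) falls from 0.81 to 0.76 one-sided, or from 0.70 to 0.65 two-sided. Holding 29 evaluable per arm and joint would need about 168, 179 or 193 recruits at f = 10, 20 or 30%.

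**6. Power if everyone is kept.** At f = 20% the effect is 8 points. With 29 per arm and joint, power is 0.64 one-sided or 0.51 two-sided. Pooled, with 58 per arm, it is 0.81 two-sided.

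**The case against.** A reader might infer that the result is certain to be inflated in favour of the app. The documents do not support that. They give no non-download rate and no prognosis for non-downloaders. If d = 0 and the app does nothing, there is no bias. At d = 2, pooled two-sided type I error stays between 5.1% and 5.4%. The sign would reverse if non-downloaders did better.

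The planned ANCOVA adjusts for age, BMI, baseline pain, anxiety, comorbidities, physical activity and social support, among others. That would absorb part of any gap, so the unadjusted figures are upper illustrations. But engagement and digital skill are not among the listed covariates, and an unadjusted t-test is also planned.

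The arms are not wholly unlike in digital demands. Both require a smartphone, and both collect the 3-month outcome through an e-mailed link. This narrows the contrast but does not create a control counterpart to the download rule.

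The hypothesis concerns patients who use the app, and the article states openly the rule, its reason and its effect on generalisability. Estimating the effect in users is a legitimate aim. However, the proper comparison is then with controls who would have used the app, and the design does not identify them. Disclosing the limitation also leaves the intention-to-treat sentence in place.

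Finally, it is tempting to blame the exclusion for two-sided power below 0.80. The step from 0.80 to 0.70 comes from the unstated sidedness. Only the further fall to 0.65 comes from non-download.

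**Conclusion.** The contradiction is explicit and needs no assumption: the analysis set cannot be both all assigned patients and the set left after two post-assignment exclusions. The download rule is also a one-arm filter. That it favours the app is probable rather than shown. The article's own rationale implies that non-downloaders gain less, and they may have a poorer prognosis.

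Its size is unknown. Under the assumed ranges and before adjustment, bias with no app effect runs from zero to 3.0 points, against a target of 10. Which type I range applies depends on whether the joints are analysed separately, as the sample size section intends, or pooled. The missing allowance for non-download is a definite gap; its cost at 20% is modest.

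This should be corrected before the analysis, because it determines who enters the primary comparison.

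**What to change.** - Remove failure to download, and post-surgical complications, as grounds for exclusion from the primary analysis set.
- Collect the t1 to t4 questionnaires from every assigned patient and analyse all of them in their assigned group as the primary analysis.
- Report the downloaders-only and complication-free comparisons as secondary per-protocol analyses, beside the planned reasons for non-use.
- If the exclusions are kept, drop the intention-to-treat claim, label the analysis per-protocol, and add a non-download allowance to the sample size.
- State the sidedness, and restate power for the diluted effect.

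The practical cost is small. These patients have consented, have baseline data and would be interviewed anyway; t1 to t3 are collected on hospital tablets and t4 online. According to the trial status section, control recruitment was still running and the app was in final testing, so intervention follow-up could still be arranged.

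The statistical cost is not small per joint: 0.64 one-sided or 0.51 two-sided at 20% non-use with no benefit in non-users. Keeping patients with complications gives back only a few (160 × 0.80 × 0.96 = 122.9 analysed, against 160 × 0.7296 = 116.7). The sponsor should choose between a larger sample and a pooled primary analysis, and state the power that goes with the choice.

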### Control group

The control group will receive standard care as provided by their hospital. This consists of verbal information about the perioperative treatment. Some clinics provide specific folders about the surgery process.

### Intervention group

Patients assigned to the intervention group will, in addition to standard care, receive the smart phone app “RECOVER-E” for iOS and Android devices. Immediately after the baseline data collection (4–6 weeks before surgery, t_0_) participants will receive an access link and instructions on how to download the app on different smartphones. Additionally, they have the possibility to get help from the project coordinators or via the study hotline. Patients register themselves with a personal ID and can immediately start using the app.

### Intervention

Four different stages in the process of knee or hip replacement have shown to be fundamental: the preoperative phase, the intra- and postoperative phase, the rehabilitative phase and the home environment [27].

RECOVER-E accompanies patients throughout the entire treatment process and with integrated gamification playfully encourages them to acquire useful knowledge and engage in exercises and self-management tasks in preparation of their surgery and everyday life after surgery. Provided information and given tasks are adapted to all 4 stages of treatment.

### App development

Considering the possibilities of mobile app design and programming, an iterative development approach of RECOVER-E intended to integrate patient experiences, the expertise of clinicians, and the results of various rapid literature reviews [28].

At an early stage of the app development 3 people over the age of 65 with experience in THR or TKR were interviewed regarding user needs based on their own surgery experience. Important results of these interviews were, for example, discovering that outpatient rehabilitation requires a very early adaptation to the home situation which was apparently difficult without assistance. Physicians, pain nurses and a physiotherapist were consulted specifically in regards to developing appropriate exercises and training recommendations, but also to identify the questions they often experience while treating patients after THR or TKR. To optimize user experience, an expert for app-development was consulted.

Rapid reviews were conducted on the following topics:
pain management before and after surgery,styles, frequencies and potential effects of self-observation and success-tracking of pain, activity or emotional statusdietary implications of OA and surgerymotivational features for increase of long-term user engagement

After the first design and functional drafts via Mock-Ups, RECOVER-E had to be streamlined for full process functioning, usability with various use cases in mind, and positive user experience [29].

The prototype of RECOVER-E was tested by conducting a live observation with 4 different users matching the target group. During the whole process of getting the app into operation and manoeuvring through the different options, the user’s view of the smartphone was filmed by a small camera worn around their neck. Users were instructed to read out aloud what appeared on their screen and encouraged to verbally express their first impressions, decisions and thoughts to the interviewer that also sat in the room [30].

Interview transcripts and video-material were analysed by content analysis with a strong focus on usability and the users’ affective reactions and decisions while using the app. The timespan analysed was the first 45–60 min of user experience. Results were used to enhance app functions and design.

### App content

To grant individualised app content, users indicate the joint that will be operated on and their date of surgery at the beginning of the RECOVER-E use. Furthermore, they will be required to specify the date of discharge as well as the beginning and end of their rehabilitation. The content of the app will automatically adjust according to the specific information provided.

The app is comprised of the following features:
Information and educationMotivationSelf-monitoringReminderCommunication

#### Information and education

Comprehensive text and video material aim to educate the patients and provide information on the disease, the artificial joint, the joint replacement procedure and everyday life after surgery. The preoperative phase focuses on information on the physiology of knee or hip, osteoarthritis, as well as, pain and pain management, but also gives a preview of daily activities with an artificial joint and support possibilities.

Patients will be prepared for the hospital stay and surgery by giving information on how to deal with allergies, general preparation for surgery, medication especially on pain and other pain management interventions [27].

The intra- and postoperative phase contains information on the hospital stay and the procedure itself, complications and how to prevent them, wound care, bowel function and body hygiene.

In the rehabilitative phase and home environment, users are encouraged to take part in their pain management, as well as, in their wound and scar care by frequent monitoring with the tools provided in the app. They are given information on rehabilitation, sports, sleep, sexual activity and returning to work post surgery. Users are offered 8 video clips with short and simple exercises to train muscles and increase flexibility in the legs for either knee or hip surgery (e.g. seated leg extension, elevation of legs while sitting) [31].

RECOVER-E proposes a certain number of repetitions and sets per exercise, which gradually increase after hospital discharge and after rehabilitation to keep training motivationally attractive. However, users are requested to first consult their physiotherapist to individually decide on the appropriate exercise intensity at any stage.

Since emotional well-being is closely and positively linked to the experience of control over one’s own recovery process, RECOVER-E provides important information on symptoms and self-management in the immediate postoperative phase. The app also motivates users to ask family and friends for support in order to bridge difficult and frustrating time periods during the first weeks after surgery [32].

Overall RECOVER-E’s education abilities aim to prepare users for an everyday, joint-sensitive life after their joint replacement surgery.

Text and video material have been developed based on findings of rapid literature reviews and enhanced by expert advice of an orthopaedic surgeon, a physiotherapist, and pain and nursing experts (see App development).

Written and spoken texts use a plain language style and refrain from technical terms or, where absolutely necessary, provide an explanation. To enhance understanding and overall user experience in larger text passages, pictures were selected to elucidate the corresponding subject.

#### Motivation

The motivation of users to a) interact with the app on a regular basis and b) to adhere to app suggestions and tasks is an important aim of the app. As a motivational feature, a daily notification will encourage users to acquire information, engage in exercises according to the treatment stage or congratulates them for special accomplishments. Additionally, the app will comprise gamification by leading the user through various achievement levels resulting in awards.

#### Self-monitoring

Users are constantly encouraged to set and achieve their own goals regarding relevant parameters like pain, physical activity, nutrition and social interaction. They can select from a number of given goals in the “aim section” of the app. These goals were developed according to strict principles of achievability and therapeutic appropriateness and are optional for users.

In the “data collection section” users have the opportunity to enter data for monitoring goal parameters. Goal-setting and self-monitoring widen the users’ reflection on their situation and progress will be visible through graphs in the app throughout all 4 phases.

#### Reminder

Constant continuity of training, frequent self-monitoring of the recovery process and possibilities for self-managing pain are the key elements requiring daily reminders. Medical professionals also see the need to enhance a patient’s self-management ability, particularly when it comes to pain and wound observation to prevent unnecessary readmissions to the hospital [32–34].

One push notification per day reminds users either to do physical exercises, read specific information relevant to the current phase, set new goals or record self-monitoring parameters. The start screen of the app additionally provides icons for pending tasks in the sections “exercise”, “information” and “data collection”. The reminder function is especially important during phases when there is reduced contact with health care professionals, such as before surgery or after the rehabilitation programme. How users experience the effect of reminders on their engagement with the app during the post-hospital phases will be analysed in the qualitative part of the pabee project.

#### Communication

The app comprises an interface for the clinical care teams. This will be used by participating hospitals to provide customized information on centre-specific procedures, teams and other information, the hospitals want to share regarding the organisation of the surgery and hospital stay. Additionally, health data provided by users in their app-based monitoring can be transferred to a specific web site accessible only by clinicians of the participating wards. Users have to give individual permission to transfer information from the pre-hospital and hospital phase only. That information can support the problem-centred conversations with nurses and doctors and give insight on pain- and function-based problems during the preparation phase of the surgery and after the operation.

Another feature to facilitate communication after discharge is an automatic message service to inform the users’ orthopaedist in case of complications after discharge: back at home users are instructed to continue self-assessment of pain, function and to observe their wound. If thresholds are exceeded, the app offers to inform the orthopaedist via fax. Users are free to decide on each individual occasion whether or not that information should be sent to their orthopaedist. They are told to visit a doctor immediately in case they observe a further decline in their health.

